Hence, the limited number of studies investigating the effectiveness of treatments for young individuals with Complex PTSD underscores the need for further research [10]. In their position paper published in 2019, the ISTSS deemed treatment recommendations premature because of current knowledge gaps. This indicates a pressing requirement for research exploring the effects of trauma-focused treatment on adolescents with (symptoms of complex) PTSD resulting from (repeated) sexual abuse, maltreatment, and/or domestic violence. To address this research gap, the present study describes an RCT aimed at investigating the differences in treatment effects between two treatment approaches (i.e., phase-based versus immediate trauma-focused) in adolescents with (symptoms of complex) PTSD resulting from a history of repeated sexual and/or physical abuse during childhood.

The primary objective of this study is to compare the results of phase-based treatment with those of immediate trauma-focused (i.e., eye movement desensitization and reprocessing; EMDR) therapy using a two-arm randomized controlled trial design. The first aim is to determine whether immediate trauma-focused treatment is not worse than phase-based treatment in reducing PTSD symptoms. If trauma-focused treatment is found to be equally effective when applied, it could lead to significant reductions in treatment duration. Second, we aim to investigate whether the phase-based therapy approach yields superior outcomes compared to the direct trauma-focused condition in terms of Complex PTSD symptoms, including emotion regulation, interpersonal problems, and self-esteem. Additionally, we will examine comorbid symptoms and dropout rates as secondary outcome measures. The third objective of the current study is to identify potential moderators and predictors of dropout or treatment responses/non-responses under both treatment conditions. We hypothesize that the presence of affect dysregulation and interpersonal problems at the beginning of therapy will be associated with poorer outcomes in the direct trauma-focused condition. Finally, we will examine the relationship between the reduction of posttraumatic stress symptoms in adolescents and a decrease in self-reported parental/caretaker stress. This objective addresses the clinical assumption that managing parental stress should be prioritized before initiating PTSD treatment in adolescents.

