### Sample size and power

This study implemented a non-inferiority trial. A non-inferiority trial is a type of clinical research study that aims to demonstrate that a (new) treatment is not worse than an existing treatment by a prespecified margin. Because the non-inferiority margin for CAPS-CA-5 scores had not yet been determined at the start of this study, we used the article published by Sloan et al. [44] to estimate the non-inferiority margin. The primary outcome was the total score on the Clinician-Administrated PTSD Scale for DSM-5 (CAPS-5). Non-inferiority was defined as a score of 10 points. However, the results showed that during follow-up, a non-inferiority margin of five points would have been sufficient to yield the same conclusion. Therefore, based on the article by Sloan et al. [44] and clinical reasoning, the largest clinically acceptable effect to declare non-inferiority is a change in the CAPS-CA-5 score of five points (d). Based on the study by Sloan and colleagues, the true mean difference (μ_B_-μ_A_) between the treatments is -1.82 (after 12 weeks). In a non-published pilot study of 17 adolescents, we calculated a mean total score on the CAPS-CA-5 of 38.2 with a standard deviation of 10.4 (σ). An equal number of participants will be included in both arms of the trial (r = 1).

For the estimation of the sample size (for 80 percent power and type 1 error of 2,5 percent) the following formula is used [45].$${n}_{A}=\frac{7.85{\sigma }^{2}\left(r+1\right)}{{\left(\left({\mu }_{B}-{\mu }_{A}\right)-d\right)}^{2}r}$$

According to this formula, 36,5 participants per arm are required. As in the previous sample size calculation, we used the baseline variables as covariates. Based on Borm et al. [46, 47] we estimate that the design factor will be equal to 0.75, because we assume a correlation of 0.5 between the two measurements. Hence, we would need 36.5*0.75 = 27.4 participants per group. To compensate for an unknown clustering effect and unknown psychometric properties, and given the need to compensate for an expected dropout rate, we plan to include 40% more participants (76 participants in total), so that 38 participants will be recruited per arm.

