### Statistical analysis

Data will be analyzed using SPSS V.29.0 for Windows (SPSS Incorporated). Pretreatment group differences with respect to age, sex, ethnicity, and type of traumatic event will be assessed using independent-sample t-tests for continuous data and χ^2^ tests for categorical data. Before testing, we will check all the data according to the appropriate assumptions.

To answer the primary question, a repeated-measures ANCOVA will be conducted. Baseline scores will be included as covariates, time as a categorical variable, and treatment condition as a fixed effect. The intercept will be treated as a random effect. We will examine the residuals to assess the model assumptions and goodness-of-fit. *P-values* will be reported to four decimal places, with *P-values* less than 0.001 reported as *p* < 0.001. For all tests, we will use 2-sided *P-values* with alpha =  < 0.05 level of significance. As this is a non-inferiority trial, both intention-to-treat and per-protocol analyses will be performed.

To evaluate the secondary outcomes, a repeated-measures ANCOVA will be conducted for the total score on the ECR-RC, DERS, RSES, RCADS, CPTCI, CBCL, OBVL, and Y-OQ-30. Baseline scores will be included as covariates, time as a categorical variable, and treatment condition as a fixed effect. The intercept will be treated as a random effect. We examine the residual to assess the model assumptions and goodness-of-fit. Delta-scores for pre- to post-treatment (T1 and T3) will be calculated, and an independent sample t-test will be used to compare the TRAP + EMDR and EMDR-only conditions. For the calculation of effect sizes (Cohen’s *d*) for within-group effects, we will divide the difference in means between pre- and post-treatment by the standard deviation of the difference in means. *P-values* will be reported to four decimal places, with *P-values* less than 0.001 reported as p < 0.001. For all tests, we will use 2-sided *P-values* with alpha =  < 0.05 level of significance.

To determine PTSD symptom changes on the CRIES-13, we will analyze the data for all time points in a linear mixed model. Time, treatment condition, the interaction term time × treatment condition, and sex will be entered as fixed factors, and age as a covariate in the model. The impact of missing data on outcome measurements will be evaluated using different methods, such as Last Observation Carry Forward (LOCF) and Multiple Imputation (MI).

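### The 5-point non-inferiority margin sizes the trial but never enters the stated primary analysis, whose P-value tests a zero difference

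*Protocol article*

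**What the plan says.** The Background section of the Protocol article gives the primary purpose: "The first aim is to determine whether immediate trauma-focused treatment is not worse than phase-based treatment in reducing PTSD symptoms".

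Sample size and power names the design as non-inferiority and sets the threshold: "the largest clinically acceptable effect to declare non-inferiority is a change in the CAPS-CA-5 score of five points (d"). The calculation there is made "for 80 percent power and type 1 error of 2,5 percent".

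Statistical analysis assigns a repeated-measures ANCOVA to the primary question, with baseline as covariate, time as a categorical variable, treatment condition as a fixed effect and a random intercept. The inferential rule is: "For all tests, we will use 2-sided *P-values* with alpha" at 0.05. The same rule is repeated for the secondary outcomes. The only element of that section specific to non-inferiority is the choice of analysis sets: "As this is a non-inferiority trial, both intention-to-treat and per-protocol analyses will be performed".

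**The concern.** The treatment P-value from an ANCOVA tests the null hypothesis that the adjusted difference is zero, unless another null is stated. None is. The question the trial was sized for has a different null: that EMDR-only is worse by 5 points or more. The section that says how the primary question is answered therefore gives a rule for a different hypothesis. It supplies no confidence limit to hold against the margin.

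The secondary questions on complex PTSD symptoms are framed in the Background as superiority of the phase-based arm, and a two-sided P-value suits them. Giving the primary outcome the same rule leaves a reader of the results with only significant or not significant. The Background also says that a finding of equal effectiveness could shorten treatment considerably, and a non-significant P-value is easily taken for such a finding. The trial's main conclusion is what is at stake.

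**Working it through.** **Inputs, all from Sample size and power:** margin d = 5; assumed true difference -1.82; SD 10.4 (pilot of 17 adolescents); type 1 error 2.5%; power 80%; r = 1; design factor 0.75; 40% inflation.

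**1. Reproduce the plan's sample size.**
- n per arm = 7.85 × 10.4² × 2 / (-1.82 - 5)² = 36.5.
- The constant is (1.960 + 0.842)² = 7.85, so the calculation is a one-sided 2.5% test against the margin. A one-sided 5% test would give 29 and does not match.
- 36.5 × 0.75 = 27.4; 27.4 × 1.4 = 38.3, stated as 38 per arm (76 in total).

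The figures reproduce. The sizing is coherent as a non-inferiority calculation.

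**2. Standard error of the adjusted difference** (normal approximation, one time point, difference = EMDR-only minus TRAP+EMDR, positive = EMDR-only worse).
- SE = 10.4 × √0.75 × √(2/n).
- n = 27.4: SE = 2.43, 95% half-width 4.77.
- n = 38: SE = 2.07, half-width 4.05.

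**3. Reading A: P > 0.05 is taken as not worse.** The chance of passing at true difference δ is Φ(1.96 - δ/SE) - Φ(-1.96 - δ/SE).

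| True difference | 27.4 per arm | 38 per arm |
|---|---|---|
| 5 points worse | 46% | 32% |
| 3 points worse | 77% | 69% |

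The intended rate at 5 points is 2.5%. Without the design factor, the 5-point row becomes 57% and 45%.

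**4. Reading B: a significant result favouring EMDR-only is required.** Power at -1.82 is Φ(-1.96 + 1.82/SE).
- n = 27.4: Φ(-1.21) = 11%.
- n = 38: Φ(-1.08) = 14%.

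The plan intends 80%.

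**5. Rule that matches the sizing: upper 95% limit below +5.** The chance of concluding non-inferiority is Φ((5 - δ)/SE - 1.96).
- At δ = 5: 2.5% for either n.
- At δ = -1.82: 80% with 27.4 per arm, 91% with 38 per arm.

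The existing sample size already supports this rule.

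**The case against.** The strongest reply is that the article should be read as a whole. Sample size and power fixes the margin as the threshold for declaring non-inferiority, the Discussion repeats the idea of a prespecified margin, and Statistical analysis calls the trial a non-inferiority trial. The planned ANCOVA also yields an adjusted difference and its standard error, so the margin comparison can be made from it. All of that is true, and it keeps the repair small. It does not remove the point, because the article does not leave the inferential rule to another document. It states one, for all tests, directly after naming the model for the primary question, and that rule does not contain the margin.

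Several stronger readings are tempting and are not supported:

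- *A reader might infer that two-sided 0.05 conflicts with the 2.5% used for sizing.* It does not. A two-sided 95% interval held against a margin is a one-sided 2.5% test.
- *A reader might infer that the stated analysis cannot show non-inferiority at all.* A significant result favouring EMDR-only would imply it. At the planned size and assumed difference, that is merely unlikely (Reading B).
- *A reader might infer that the plan intends to read non-significance as not worse.* The article says nothing of the kind. The 32% to 46% figures are conditional on that reading.
- *A reader might infer that EMDR-only could be significantly worse with its interval still inside the margin.* At these standard errors the full interval is at least 2 × 4.05 = 8.1 points wide, so it cannot lie wholly between 0 and 5.
- *A reader might count it as an error that no rule says both analysis sets must meet the margin.* A statistical analysis plan that is not shown may settle this.

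**Conclusion.** The point stands in this form: the margin that defines and sizes the trial is absent from the stated primary analysis, and the P-value rule given there addresses a zero difference. This is a mismatch between two sections of the same document, not detail left for later.

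Under either natural use of the stated rule, the operating characteristics depart from the design. The false-claim rate at the margin is 32% to 46% instead of 2.5%, or power is 11% to 14% instead of 80%.

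These sizes rest on SD 10.4, the 0.75 design factor, a single-time-point standard error and 27.4 to 38 evaluable participants per arm. The upper end assumes no loss to dropout or clustering, although the 40% inflation was added partly for those. A repeated-measures estimate averaged over time would have a somewhat different standard error. The -1.82 is taken to favour EMDR-only, as the sizing formula implies.

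**What to change.** In Statistical analysis, replace the P-value rule for the primary outcome with wording such as: *Non-inferiority is concluded if the upper limit of the two-sided 95% confidence interval for the adjusted CAPS-CA-5 difference (EMDR-only minus TRAP+EMDR) is below +5 points.* Keep two-sided P-values for the secondary superiority questions.

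The sponsor should settle two further matters in the same paragraph:

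- **Time point.** The article compares the arms at post-treatment and at six months, and Statistical analysis names neither as primary. The sponsor should name one (T3, for example). If it is a single visit, the model needs a time-by-treatment term. As listed, the primary model has none and estimates an effect averaged over visits.
- **Analysis sets.** Confirm how the intention-to-treat and per-protocol results combine, here or in the statistical analysis plan.

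The cost is one paragraph and, for a single visit, one extra model term. No new data are needed and the sample size is unchanged. The change should be made before the primary analysis is run.

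### Secondary outcomes get two unranked between-arm tests at two-sided 0.05, and the added T1–T3 change-score t-test is the less precise of the two

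*Protocol article*

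**What the plan says.** The secondary-outcome paragraph of the Statistical analysis section opens with the model: "To evaluate the secondary outcomes, a repeated-measures ANCOVA will be conducted for the total score on the ECR-RC, DERS, RSES, RCADS, CPTCI, CBCL, OBVL, and" (the list ends with the Youth Outcome Questionnaire). Its terms are given as follows: "Baseline scores will be included as covariates, time as a categorical variable, and treatment condition as a fixed effect". The intercept is random, and no time × treatment interaction is listed.

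The same paragraph continues: "Delta-scores for pre- to post-treatment (T1 and T3) will be calculated". For comparing the arms on these scores, it specifies that "an independent sample t-test will be used to compare the TRAP + EMDR and EMDR-only conditions". Within-group effect sizes follow. The paragraph closes with a common rule, "For all tests, we will use 2-sided" P-values at the "0.05 level of significance". It does not call either between-arm comparison main, supportive or descriptive.

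Two other sections bear on this. Sample size and power takes a design factor of 0.75 for baseline adjustment of the primary outcome, "because we assume a correlation of 0.5 between the two measurements". The Background gives the second aim as investigating "whether the phase-based therapy approach yields superior outcomes compared to the direct trauma-focused condition in terms of Complex PTSD symptoms", that is, emotion regulation, interpersonal problems and self-esteem.

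**The concern.** The same data on the same scale would yield two P-values for the difference between arms. With no order between them, the choice of which to believe could be made after both are seen. The aim most exposed is the second one, where a superiority statement for phase-based treatment rests on secondary scales.

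The two tests are also unequal in quality. The change score subtracts the whole baseline value, whereas ANCOVA subtracts only the part that predicts the outcome. The sample-size section takes credit for the gain from baseline adjustment on the primary outcome; the delta-score t-test gives that gain up on the secondary ones.

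**Working it through.** **Inputs.** From Sample size and power: SD 10.4, margin 5, assumed difference −1.82, correlation 0.5, design factor 0.75, 38 per arm. From Statistical analysis: two-sided 0.05 for each test. The correlation is stated for the CAPS-CA only; using it for the secondary scales is an assumption, so a range is shown.

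**The plan's own figure.** 7.85 × 10.4² × 2 / (−1.82 − 5)² = 36.5 per arm. Times 0.75 = 27.4. Times 1.4 = 38.3, planned as 38. This reproduces, and 0.75 = 1 − 0.5² is the ANCOVA variance factor.

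**Precision at T3.** With equal SDs at baseline and T3 and correlation ρ, the variance factors relative to an unadjusted T3 comparison are:
- baseline-adjusted: 1 − ρ²
- change score: 2(1 − ρ)
- ratio: 2/(1 + ρ)

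| ρ | Adjusted | Change score | Ratio | CI width ratio |
|---|---|---|---|---|
| 0.3 | 0.91 | 1.40 | 1.54 | 1.24 |
| 0.5 | 0.75 | 1.00 | 1.33 | 1.15 |
| 0.7 | 0.51 | 0.60 | 1.18 | 1.08 |

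At 0.5 the change-score factor is 1.00, so it is no better than ignoring baseline. At 0.9 the ratio falls to 1.05. The direction does not depend on equal SDs: the change-score variance minus the adjusted variance equals (SD₀ − ρ·SD₁)², where SD₀ and SD₁ are the baseline and T3 SDs. This is never negative. The one degree of freedom spent on the covariate is negligible with 76 participants.

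**Power.** At ρ = 0.5 and 38 per arm, the effect detectable with 80% power is 0.56 SD adjusted and 0.64 SD for the change score. At the effect where the adjusted test has 80% power, the t-test has 68%.

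**Baseline imbalance.** The standard error of the baseline difference is √(2/38) = 0.23 SD. The change score removes all of a chance difference where a fraction ρ is warranted. At ρ = 0.5, a one-standard-error imbalance moves its estimate by (1 − 0.5) × 0.23 = 0.11 SD away from the adjusted one.

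**Error from having two tests.** The two estimators correlate √[(1 − ρ²)/(2(1 − ρ))] = √0.75 = 0.87 at ρ = 0.5. From the bivariate normal under no difference, the chance that at least one test is significant is 7.3% (7.2% in a simulation of 40,000 trials with 38 per arm). It is 8.0% at ρ = 0.2 and 6.0% at ρ = 0.9. If the ANCOVA effect averages T3 and T4 with all correlations 0.5 (an assumption), it is 8.3%. Two independent tests would give 9.75%.

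**Disagreement.** At ρ = 0.5 and the effect where the adjusted T3 test has 80% power, exactly one of the two tests is significant in about 17% of trials (23% at ρ = 0.3, 11% at ρ = 0.7).

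**Different targets.** Without a time × treatment term, the ANCOVA treatment effect is averaged over the post-baseline times, while the t-test concerns T3 alone. The tests can therefore differ for reasons other than noise.

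**The case against.** The best defence is that the ANCOVA is introduced as the means of evaluating the secondary outcomes, and that the delta-scores come just before the within-group effect sizes, so they may be meant as supplementary pre–post reporting. That reading is possible, but the text names a between-arm test and puts it under the same 0.05 rule. It is also fair that a separate analysis plan could rank the tests. The point here is narrower: the article itself specifies an inferior second test, which is more than a missing detail.

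The t-test is also the only T3-specific between-arm comparison stated. That stands, and it shapes the fix.

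Several stronger readings are tempting and not supported:
- *The t-test uses complete cases only.* The article does not say so, and it plans last-observation-carried-forward and multiple-imputation checks of missing outcome data.
- *Eight outcomes are each tested twice.* Table 1 as printed marks the CBCL at one time point per arm, so no delta can be formed for it.
- *The plan loses a quarter of its information.* That would follow at ρ = 0.5 only if the t-test decided; the ANCOVA remains in the plan.
- *Family-wise error is 34% for eight outcomes (1 − 0.95⁸) or 19% for four (1 − 0.95⁴).* These figures come from having several outcomes, assume independence, and would remain if the t-test were deleted.
- *A Holm correction is required.* Multiplicity control for secondary outcomes is a debatable choice, commonly left to the analysis plan.

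**Conclusion.** The point holds for the secondary outcomes. The article sets two unranked between-arm tests side by side, and the second is never the more precise in large samples. The size is moderate: a variance ratio of 1.33 and a confidence interval about 15% wider if ρ = 0.5 carries over from the primary outcome (ratio 1.54 at 0.3, 1.18 at 0.7), and a false-positive risk per outcome of about 7% in place of 5% if either test may count. The more practical harm is that the tests can give different verdicts on the superiority aim with no stated rule for which stands. These figures rest on a single post-baseline time, approximate normality and equal SDs at baseline and T3; the direction of the precision loss does not need equal SDs. The primary non-inferiority test and the sample size are not touched.

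**What to change.** Add a time × treatment term to the planned baseline-adjusted repeated-measures model. Take the T3 between-arm contrast with its 95% CI from that model, and name it as the sole between-arm test at T3 for each secondary outcome measured after treatment. Delete the delta-score t-test, or keep delta-scores as descriptive summaries without a between-arm P-value.

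Deleting the t-test alone would not be enough, because the model as written gives no T3-specific contrast. The cost is one extra model term. No further data or participants are needed, and the article describes the study as ongoing, so the change can be recorded before analysis.

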### Primary outcome

#### The clinician-administered ptsd scale for children and adolescents

The Clinician-Administered PTSD Scale for Children and Adolescents (CAPS-CA) [24] is a structured clinical interview used to establish the diagnostic status of the DSM-IV and DSM-V criteria for PTSD. The interviewer can rate the frequency and intensity of each symptom on a five-point Likert scale. Furthermore, each symptom can be rated as present or absent, as proposed by Weathers, Ruscio, and Keane [25] to score a symptom as being present. The CAPS-CA can be reliably administered by different interviewers. The Dutch CAPS-CA showed as good internal consistency, inter-rater reliability, convergent and divergent validity, and concurrent validity as the original English version [26]. The CAPS-CA will be administered three times (T1, T3, and T4) for adolescents in the EMDR-only group and four times in the TRAP + EMDR group (T1, T2, T3, and T4). Adding the CAPS-CA at T2 in the TRAP + EMDR condition will provide information about the effects and necessity of skills training TRAP as a standalone treatment.

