### Other measurements

#### Children's revised impact of event scale

The Children's Revised Impact of Event Scale (CRIES-13) [42] is a brief self-report questionnaire designed to screen for PTSD in children aged 8 years and older. It consists of 13 questions assessing posttraumatic intrusions, avoidance, and arousal. Children rated the frequency with which they had experienced each item during the past week using a four-point Likert scale (0 = not at all, 1 = rarely, 3 = sometimes, 5 = often). Psychometric properties have been previously reported [42], showing that the CRIES-13 is a valid measure of posttraumatic stress. In this study, the internal consistency of the CRIES-13 was 0.89. In this study, the CRIES-13 will be used to measure posttraumatic stress symptoms between each session during the course of treatment.

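### The CRIES-13 mixed model is valid but omits any baseline PTSD severity term, so it gives up some precision that a score already collected could supply

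*Protocol article*

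**What the plan says.** The Statistical analysis section of the protocol article specifies repeated-measures ANCOVAs for the primary and secondary outcomes. For both it states: "Baseline scores will be included as covariates, time as a categorical variable, and treatment condition as a fixed effect".

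For CRIES-13 it states "we will analyze the data for all time points in a linear mixed model" and then lists the terms: time, treatment, their interaction "and sex will be entered as fixed factors, and age as a covariate in the model". Nothing elsewhere in the article adds a baseline PTSD score to this model.

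Three other places bear on the point:

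- The sample size section relies on baseline adjustment for CAPS-CA-5: "we estimate that the design factor will be equal to 0.75, because we assume a correlation of 0.5 between the two measurements".
- Table 1 marks CRIES-13 only in the each-session column, in both arms, and not at T0 or T1. The instrument's own section says "the CRIES-13 will be used to measure posttraumatic stress symptoms between each session during the course of treatment", and describes the recall window thus: "Children rated the frequency with which they had experienced each item during the past week".
- CAPS-CA is taken at T1 in both arms; for the shorter arm, "The CAPS-CA will be administered three times (T1, T3, and T4) for adolescents in the EMDR-only group". The Randomization section places completion of the T0 and T1 measures before allocation is released.

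**The concern.** Time is a categorical factor in the CRIES-13 model. With a free treatment effect and a free interaction, the two arms may have any means at every session, including the first. No pre-randomisation information on PTSD severity enters. Each arm comparison is then either a plain difference at a session or a difference in change from session 1. Where a baseline severity score predicts the later scores, a baseline-adjusted comparison is more precise.

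The protocol applies this principle to its other repeated-measures models. It matters somewhat here because CRIES-13 is the only PTSD measure followed through treatment in both arms: the mid-treatment CAPS-CA is taken only in the phase-based arm. With 76 participants planned, the intervals on that comparison may be wider than they need be.

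**Working it through.** **The plan's own figure.** Inputs from the sample size section: SD 10.4, margin 5, assumed difference -1.82, r = 1, multiplier 7.85.

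- n per arm = 7.85 × 10.4² × 2 / (-1.82 - 5)² = 1698.1 / 46.51 = 36.5, as stated.
- Design factor with correlation 0.5: 1 - 0.5² = 0.75, giving 36.5 × 0.75 = 27.4, as stated.
- 27.4 × 1.4 = 38.4, stated as 38 per arm.

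So the protocol itself values baseline adjustment at a 25% cut in variance, for CAPS-CA-5. It states no figure for CRIES-13.

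**If session 1 were a true pre-treatment baseline.** Assume 38 per arm, complete data on sessions shared by both arms, a common SD σ, and correlation ρ between session 1 and session k. In units of 2σ²/n:

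- plain difference at session k: 1
- difference in change from session 1: 2(1 - ρ)
- difference adjusted for session 1, or with the arms constrained equal there: 1 - ρ²
- adjusted relative to change: (1 - ρ²) / [2(1 - ρ)] = (1 + ρ)/2

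| ρ (assumed) | plain | change | adjusted | adjusted / plain | adjusted / change |
|---|---|---|---|---|---|
| 0.3 | 1.00 | 1.40 | 0.91 | 0.91 | 0.65 |
| 0.5 | 1.00 | 1.00 | 0.75 | 0.75 | 0.75 |
| 0.7 | 1.00 | 0.60 | 0.51 | 0.51 | 0.85 |

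At ρ = 0.5 the standard error of the plain difference is √(2/38) = 0.229 SD, and the adjusted one is 0.229 × √0.75 = 0.199 SD.

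**If correlation decays.** The table applies at every session only if ρ is constant, as a random intercept implies. Under first-order autoregressive decay with lag-1 correlation 0.5, the correlation between sessions 1 and 12 is 0.5¹¹ ≈ 0.0005. The adjusted variance is then 1.00 of the plain difference, which is no gain, but (1 + 0.0005)/2 = 0.50 of the change contrast. With lag-1 correlation 0.9, 0.9¹¹ = 0.314; the ratios are 1 - 0.314² = 0.90 and 1.314/2 = 0.66.

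**If T1 CAPS-CA is the covariate.** Let r be its correlation with CRIES-13 at a session (not given in the article).

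- As a main effect with the same r throughout, it multiplies the variance of a session difference by 1 - r²: 0.91, 0.75 or 0.51 for r = 0.3, 0.5 or 0.7.
- It leaves the change contrast unaltered, because a constant term cancels in a within-person difference.
- With an interaction with time, the change contrast is multiplied by 1 - (r_k - r_1)² / [2(1 - ρ)]. This is 1.00 when r_k = r_1. With r_1 = 0.7, r_k = 0.3 and ρ = 0.5 it is 1 - 0.16/1.00 = 0.84.

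The interaction therefore helps the time-by-treatment contrast only to the extent that CAPS-CA predicts early and late sessions differently.

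**The case against.** The strongest defence is that the different model follows from a different schedule. The models that adjust for baseline use outcomes with a pre-treatment score in Table 1; CRIES-13 has none. Past-week recall makes session 1 a pre-treatment measure only if the form is completed before any session content, and the wording about measuring between sessions leaves that open. If it is completed afterwards, adjusting for it or equating the arms there could remove or distort part of the treatment effect. This stands, and it rules out treating session 1 as a ready-made baseline. It does not touch T1 CAPS-CA, which precedes randomisation in both arms.

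Second, the stated purpose is to study symptom change. The time-by-treatment term addresses that and is net of a chance difference at session 1. This also stands: a reader might infer that the planned model is biased, and it is not. The issue is efficiency alone.

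Third, a reader might infer from the 0.75 factor that adjusted data on 38 per arm are worth about 51 (38 / 0.75 = 50.7). The documents do not support that for CRIES-13. The correlation of 0.5 is stated for CAPS-CA-5, the figure needs that correlation to hold out to the session compared, and it vanishes at session 12 under the faster decay shown above.

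Fourth, a reader might say that every other outcome is baseline-adjusted. The repeated-measures ANCOVAs are, but the same section also compares secondary outcomes by t-tests on unadjusted T1-to-T3 change scores.

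Fifth, one arm has 24 sessions and the other 12, and the article names no particular session contrast as the target, so no single variance ratio describes the loss. CAPS-CA is also a different instrument, and eligibility requires PTSD on it, which may narrow its range and weaken its correlation with CRIES-13. Both points limit what can be promised.

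**Conclusion.** The point holds as a minor one. The CRIES-13 model is valid and unbiased under randomisation, but it leaves out baseline PTSD severity, which the trial collects before randomisation and uses in its primary ANCOVA.

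The possible gain is conditional. With a genuine pre-treatment session-1 score and constant correlation, the variance of a later arm difference falls to 0.91, 0.75 or 0.51 of the unadjusted value at ρ = 0.3, 0.5 or 0.7. With decaying correlation, late-session differences gain little, while the change contrast against session 1 still gains. With T1 CAPS-CA, the gain depends on a correlation with CRIES-13 that the article does not give, and may be small for the change contrast.

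CRIES-13 is listed among the other measurements. Neither the non-inferiority conclusion on CAPS-CA nor the planned 76 participants is affected.

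**What to change.** In the Statistical analysis section, add the T1 CAPS-CA score as a covariate in the CRIES-13 model. Add its interaction with time as well if the time-by-treatment contrast is the target.

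Confirm from the study procedures when the first CRIES-13 is completed. If it always precedes session-1 content, use it as the baseline instead: either as a covariate with sessions 2 onward as outcomes, or as an outcome with the arms constrained equal at session 1. The constrained form also keeps participants who lack a session-1 score. If it is completed after session content, do neither and keep CAPS-CA.

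The choice should be recorded before arm-level data are examined, so that it cannot depend on results. The cost is a line or two of text and a check of timing. The covariate uses one model coefficient, plus one per further time parameter if the interaction is included. No new data are needed.
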